### Follow up

A follow-up assessment will be performed within three years after individual’s first visit with changes of imaging presentations and other outcomes in the three groups as time goes on (up to 36 months) be compared. Individuals will come back to the medical center once half a year for countercheck. All the protocols and evaluations are the same with that they get at the first time.

### Sample size calculation and statistics

Power calculations have been estimated with reference to other studies that used similar end points [21, 29], according to the formula for estimating the variances of mean values from multiple groups [29]. A sample size of 40 patients per group will be suitable with a power of 0.8, an alpha significance level of 0.05 (two-side). In our group, longitudinal changes of this effect size have been shown previously in groups larger than 10 subjects. Given a drop-out ratio of included subjects, at 25 %, into account, the total sample size is 53 in each group.

Demographic clinical, laboratory, cognitive, and neuropsychological data will be analyzed using SPSS 22.0 (SPSS, Inc.). One-way analysis of variance or *χ*^2^ test will be used to explore differences of these data among three groups (HC, prodromal diabetes and diabetes). Neuropsychological difference among them will be performed with analysis of covariance (ANCOVA) using demographic factors (gender, age, and years of education) as covariates. *Post-hoc* comparisons will then be performed with all demographic factors (gender, age, and years of education) as covariates. *P* < 0.05 is considered as significant. It is reported ReHo and ALFF values are affected by the structure alterations (e.g., atrophy) [30]. We will take ventricular volume as a covariance to rule out such influence.

For images analysis, one-sample t tests will be performed on the individual corresponding maps for each group using SPM12 to explore the differences within groups. Dunnett-*t* test will be performed for differences among case groups and healthy control group. The statistical threshold of the two test will both be set at *P* <0.005 which corresponded to a corrected *P* <0.005 (multiple comparisons with family-wise error).

Linear regression analysis is performed across the T2DM groups and prediabetes groups to assess relationships between imaging values and cognitive testing scores. When the most sensitive parameters are found, a receiver operating characteristic (ROC) curve will be generated to achieve the sensitivity and specificity of the certain parameter for early detection of the cognitive decline.

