Previous studies suggested that the brain microvascular alterations might explain MCI. A positron emission tomography-computed tomography study revealed that the focal brain blood decrease occured at as early as several years before Alzheimer`s disease diagnosis and was accompanied with the MCI progression [16]. On the contrary, a trend to a slight cerebral blood flow (CBF) increase in bilateral hippocampi and the posterior cingulate gyrus among patients with MCI was noticed using dynamic susceptibility contrast MRI [17]. The major shortcoming of these methods to measure CBF is the use of radio-labeled contrast agents, thus, not suitable for screening brain microvascular alterations in the prodromal diabetic population. Three-dimensional pseudo-continuous arterial spin labeling (3D-pCASL), a non-invasive and non-contrast perfusion imaging method [18], is commonly used to measure CBF alterations and demonstrates equivalent diagnostic performance to Single-photon emission computed tomography (SPECT) for Alzheimer`s disease [19].

Thus, we designed the current prospective diagnostic trial for 2 purposes. First, to investigate the structure, functional alterations and gray/white matter integrity with sMRI, fMRI and diffusional kurtosis imaging (DKI, also measures non-Gaussian diffusion and may provide additional and complementary information to DTI [20]) in prodromal diabetic population, respectively. Second, to investigate the early brain microvascular alterations by using 3D-pCASL.We hope to establish an integrated diagnosing system for early MCI in prodromal diabetic population by using multimodal MRI techniques.

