## Discussion

The current study evaluates various characteristics of diabetes, especially the central nervous system image presentations in different stage of diabetes progression, and aims to establish an imaging evaluation system for detecting and evaluate MCI in diabetes. Benefits and limitations of this study are discussed below.

It is reported by most researchers that diabetes result in regional hypoperfusion. However, Henry Rusinek and his colleagues found that no hypoperfusion exists in diabetes group, in contrast to hypoperfusion in insulin resistant but not diabetes group [29]. Since insulin resistant is one of main mechanisms of diabetes, we are still uncertain why the perfusion data differs between the two groups. The current study will follow up individual’s characteristics in various areas, especially the image presentation for not less than 3 years. Natural progression of diabetes is monitored. Reperfusion or compensation result in diabetes will be explored. We may discovery the unrevealed mechanism for the divergent between IR and diabetes group.

Structure changes are common in advanced T2DM. It may also exist at prediabetes stage. The volume changes should be used to be one of the covariant to prevent its effect to signal intensity. In current study, we take cerebral ventricle volume, which may represent the structure changes of the whole brain, as a covariant. DKI reveals the non-Gaussian characteristics of gray and white matter [31]. Imaging reports of this respect in diabetes are limited. We undergo the examination of DKI, instead of DTI to explore the real world of microstructure.

Various imaging researches of diabetes have been reported. Most of them are studies of one or two protocols. In our study, multi-modal sequences will be conducted and analyzed at the same time. It may be revealed which one or combined protocols may express the highest area under curve by drawing ROC curve. Corresponding sensitivity and specificity are calculated, and then we will get the cutoff values to diagnose MCI.

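### The 80% power with 40 per group rests on a multi-group-means formula at alpha 0.05, so it does not describe the planned Dunnett image comparison of prodromal diabetes with controls at corrected P < 0.005

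*Protocol article*

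**What the plan says.** All of the following is in the Protocol article, mostly under Sample size calculation and statistics.

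- **Basis of the size.** The calculation is described in these words: "according to the formula for estimating the variances of mean values from multiple groups [29]. A sample size of 40 patients per group will be" (the claim attached is 80% power at two-sided alpha 0.05). Attrition of 25% then brings enrolment to 53 per group.
- **Effect size.** None is stated. The text says only that "longitudinal changes of this effect size have been shown previously in groups larger than 10 subjects", without a mean, SD or standardised difference.
- **Image comparison.** "Dunnett-*t* test will be performed for differences among case groups and healthy control group", at P < 0.005, described as family-wise corrected.
- **Other data.** Three-group ANOVA or ANCOVA at P < 0.05 is assigned to demographic, clinical, laboratory, cognitive and neuropsychological data.
- **Status of imaging.** The section Primary outcome measure consists of MRI measures compared across the three groups.
- **Aim.** The Background closes with: "We hope to establish an integrated diagnosing system for early MCI in prodromal diabetic population by using multimodal MRI techniques".

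**The concern.** A formula built on the spread of several group means answers whether the groups differ at all. A Dunnett test answers two narrower questions: does prodromal diabetes differ from control, and does T2DM differ from control? Power for the first does not carry over to either of the second. It depends on how the means are arranged, and the Dunnett test has its own, larger critical value. Here the significance level changes too, from 0.05 in the sizing to 0.005 in the image analysis.

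A reader is likely to take 80% as the chance of detecting a prodromal change on imaging. If the true chance is much lower, a negative prodromal map could be read as evidence of no early change when the comparison had little power to show one.

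**Working it through.** **Inputs from the article:** three equal groups, 40 evaluable per group, power 0.80, two-sided alpha 0.05, dropout 25%, Dunnett test against control, image threshold 0.005.

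**Assumptions, because the article is silent:** one scalar measure, normal data with a common SD, exactly 80% power for the overall one-way F test with 40 per group, and the image threshold read as the Dunnett family alpha for that single measure.

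**1. The plan's own figures.** Enrolment: 40 / 0.75 = 53.3, against 53 stated (53 × 0.75 = 39.75), which is adequate. The 40 cannot be reproduced forward without an effect size, so it is solved backward.

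**2. Implied effect.** Overall F test with df 2 and 117 and noncentrality λ = 120 f². Power of 0.80 at alpha 0.05 requires λ = 9.89, so f = √(9.89/120) = 0.287.

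**3. Implied difference between prodromal and control,** in SD units. f is the SD of the three means divided by the within-group SD. Means are listed as control, prodromal, T2DM.
- (0, d, 0) or (0, d, d): f = d√2/3, so d = 3 × 0.287/√2 = 0.609.
- (0, d/2, d): f = d/√6, so d = 0.703 and the prodromal difference is half of that, 0.352.
- (0, d, d/2): same range, and the prodromal difference is the full 0.703. For a fixed f this is the largest possible difference between any two of the three means.

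**4. Dunnett critical values** (two comparisons, correlation 0.5, 117 df): 2.239 at family alpha 0.05 and 3.079 at 0.005.

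**5. Contrast power.** Noncentral t with 117 df and noncentrality d√(40/2) = 4.472 d.

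| Pattern (control, prodromal, T2DM) | Prodromal difference (SD) | Noncentrality | Power at 0.05 | Power at 0.005 |
|---|---|---|---|---|
| Graded (0, d/2, d) | 0.352 | 1.57 | 25.6% | 7.1% |
| Prodromal only, or both case groups equally shifted | 0.609 | 2.72 | 68.6% | 36.6% |
| Prodromal most extreme, T2DM midway (0, d, d/2) | 0.703 | 3.14 | 81.6% | 52.8% |

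Since the last row has the largest possible difference for this f, 53% is the ceiling at 0.005.

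**6. Detectable difference.** With 40 evaluable per group, 80% power for one Dunnett contrast needs about 0.69 SD at 0.05. At 0.005 it needs about 0.88 SD: approximately (3.079 + 0.84)/4.472 = 0.88.

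**7. Sensitivity.**
- If the 40 came from a two-sample t test instead (d = 0.634), Dunnett power is about 72% at 0.05 and 41% at 0.005.
- If 0.005 is applied to each comparison without the Dunnett adjustment (critical value 2.861), the three rows become 10%, 45% and 61%.
- If nobody dropped out (53 evaluable), power at 0.05 would be about 34%, 81% and 92%, and at 0.005 about 11%, 52% and 70%.

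None of these alternatives brings the contrast to 80% at 0.005.

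**The case against.** Several points on the other side have force.

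**At alpha 0.05 there need be no shortfall.** A reader might infer that the 80% fails for the prodromal contrast whatever the truth. The article does not support that: with prodromal most extreme and T2DM midway, power at 0.05 is 82%. The shortfall holds for every pattern only at 0.005.

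**The percentages are conditional.** It is also tempting to present 69% or 26% as the trial's real power. The article gives no effect size, so f is back-solved. Reading the formula as an overall F test is an inference from loose wording, and the halved prodromal effect behind the 26% is an illustrative choice found nowhere in the text. The Discussion might seem to supply the prodromal-only pattern, since it says the study cited for the formula "found that no hypoperfusion exists in diabetes group, in contrast to hypoperfusion in insulin resistant but not diabetes group [29"]. But it presents that result as an exception to what most researchers report, and an insulin-resistant group is not the same as this trial's group defined by impaired fasting glucose or impaired glucose tolerance. It makes the pattern worth examining, no more.

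**The formula does fit part of the plan.** Three-group ANOVA/ANCOVA at 0.05 is planned for clinical and cognitive data, and the Abstract lists MoCA as a primary outcome (Secondary outcome measures lists it as secondary). The sMRI and 3D-pCASL sections also speak of comparisons among groups, the latter at corrected P < 0.05 and without naming Dunnett. So the mismatch is confined to the Dunnett image comparison, and the image threshold itself needs reconciling between sections.

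**Nothing is miscalculated.** The dropout step is sound, and sizing on an overall test before comparing with control is common practice. That stands. The defect is one of alignment: the power statement and the planned image test differ in both hypothesis and significance level. Since the article states both, this is not a detail left to a fuller document.

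**Conclusion.** The stated 80% should not be read as the power of the prodromal-versus-control image comparison. Under the assumptions listed, that power runs from about 26% to 82% at alpha 0.05 across the patterns examined, and from about 7% to 53% at the stated 0.005, where no arrangement of means reaches 80%.

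The mismatch between sizing basis and image test is plain in the text. The percentages are illustrative: they rest on the back-solved f = 0.287, a single cross-sectional measure, and the threshold taken as a Dunnett family alpha. If 0.005 also has to absorb correction over voxels, the criterion at any one voxel is stricter still.

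It does not follow that the enrolment figure is wrong or that more subjects are required. Without an effect size the article cannot show that, and a true difference of 0.88 SD or more would be detected with at least 80% power as planned.

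**What to change.** Keep 53 per group and revise the power statement as follows.

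1. Limit the 80% at alpha 0.05 to the overall three-group ANOVA/ANCOVA, and state the effect size it assumed.
2. Name prodromal diabetes versus healthy control as the image contrast to which power refers.
3. Settle one image threshold, reconciling the 0.005 in the statistics section with the 0.05 in the 3D-pCASL section, and state power for the Dunnett test at that threshold. Possible wording: with 40 evaluable subjects per group, each Dunnett comparison with healthy controls on a single measure has 80% power for a difference of about 0.88 SD at two-sided family alpha 0.005. If the threshold is reconciled to 0.05, the figure is about 0.69 SD.
4. Show the pattern-dependent powers as a conditional range, with the assumptions alongside: 26%, 69% and 82% at 0.05; 7%, 37% and 53% at 0.005.

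The cost is a few sentences and no additional subjects. The downside is a less favourable stated power for the contrast that matters most.

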**Methods:**

In this study, healthy controls, prodromal diabetes and diabetes subjects (53 subjects/group) aged 40-60 years will be recruited from the physical examination center of Tangdu Hospital. The neuroimaging and psychometric measurements will be repeated at a 0.5 year-interval for 2.5 years’ follow-up. The primary outcome measures are 1) Microstructural and functional alterations revealed with multimodal MRI scans including structure magnetic resonance imaging (sMRI), resting state functional magnetic resonance imaging (rs-fMRI), diffusion kurtosis imaging (DKI), and three-dimensional pseudo-continuous arterial spin labeling (3D-pCASL); 2) Cognition evaluation with MoCA. The second outcome measures are obesity, metabolic characteristics, lifestyle and quality of life.

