#### 3D-pCASL

According to the White Paper of the International Society for Magnetic Resonance in Medicine (ISMRM) perfusion study group [21], Perfusion images will be obtained using a 3D-pCASL technique [22] with the following parameters: 512 sampling points on eight spiral arms, TR = 4886 ms (post label delay (PLD) = 2025 ms), TE = 10.5 ms, slice number = 40, FOV = 256 × 256 mm^2^, matrix = 128 × 128, slice thickness = 2.0 mm, number of excitations (NEX) = 3, FA = 111°. The bottom of the slab should be positioned at the bottom of the cerebellum, with coverage of the entire cerebrum. This sequence is pseudo-continuous labeling, background suppression, and a segmented three-dimensional readout without vascular crushing gradients. A simplified model will be used to calculate and present both label/control difference images and cerebral blood flow in absolute units. The whole scan will cost 4 min.

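### The 80% power is stated at alpha 0.05, but the image tests behind the primary outcome are set at P<0.005, where power for the same implied effect is roughly half

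*Protocol article*

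**What the plan says.** All places are in the protocol article.

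- **Sizing** (Sample size calculation and statistics): "A sample size of 40 patients per group will be suitable with a power of 0.8, an alpha significance level of 0.05 (two-side"). The basis is described as "Power calculations have been estimated with reference to other studies that used similar end points", with a formula for means of multiple groups. Neither the endpoint nor the effect is given a value; the text says only that "longitudinal changes of this effect size have been shown previously in groups larger than 10 subjects". After 25% drop-out, "the total sample size is 53 in each group".
- **Image tests** (same section, third paragraph): one-sample t tests within groups and a Dunnett test of the case groups against healthy controls. Both use P<0.005, "which corresponded to a corrected" P<0.005 with family-wise error control.
- **Voxel-wise CBF** (3D-pCASL data analysis): group differences at a multiplicity-corrected P<0.05 with a minimum extent of 50 pixels.
- **Neuropsychological data** (Sample size calculation and statistics): tested at P<0.05.
- **Primary outcome** (Primary outcome measure): MRI differences among the three groups. The abstract also names MoCA as primary, while Secondary outcome measures lists MoCA among the mental health scales.

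**The concern.** Power belongs to a particular test at a particular significance level. Here the level used for sizing is ten times the level declared for the image tests, and those tests carry the primary outcome. Because no effect is stated, the 80% is the only figure a reader has. A null imaging result would then be read as coming from a study with an 80% chance of finding the effect, when the chance at the declared threshold was about half. The plan also carries the most sensitive imaging parameters forward to the ROC analysis. If these are picked from the thresholded imaging results, real signals may be lost before that step.

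**Working it through.** **Inputs from the document.** 40 evaluable per group, power 0.80, two-sided alpha 0.05, three equal groups, 25% drop-out, 53 recruited per group, image tests at P<0.005.

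**Not in the document.** The effect size, the SD, and the number of independent voxel tests.

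**Step 1. The plan's own figures.** Drop-out: 40/0.75 = 53.3, stated as 53, which is a rounding matter only (53 × 0.75 = 39.75). The 80% cannot be reproduced forward without an effect, so I solved for the effect that gives exactly 80% at 40 per group and alpha 0.05.

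- Two-sample t: noncentrality d√(n/2), df 78, critical t 1.991. Power 0.80 gives d = 0.634.
- Three-group ANOVA: noncentrality 3n·f², df 2 and 117, critical F 3.07. Power 0.80 gives f = 0.287.
- Dunnett, two contrasts with control, df 117, simulated critical value 2.24. Power 0.80 per contrast gives d = 0.690.

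**Step 2. The same effects at 0.005, 40 evaluable per group.**

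- t: 0.634 × √20 = 2.84 against a critical value of 2.89. Power 48.3%.
- F: 120 × 0.287² = 9.89, critical F 5.55. Power 49.2%.
- Dunnett at family-wise 0.005, simulated critical value 3.08:

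| How the effect was sized | d for the largest contrast with control | Power |
|---|---|---|
| ANOVA f, one group apart from the other two: d = 3f/√2 | 0.609 | 37% |
| Two-sample t | 0.634 | 41% |
| Dunnett | 0.690 | 51% |
| ANOVA f, evenly spaced means: d = f√6 | 0.703 | 53% |

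**Step 3. If nobody drops out (53 per group).** t: 0.634 × √26.5 = 3.27, power 65%. F: 159 × 0.287² = 13.1, power 67%.

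**Step 4. What 40 per group can detect at 0.005 with 80% power.** d = 0.84 by two-sample t, or f = 0.37 by ANOVA. Against the implied effect, 0.84/0.634 = 1.32, about 30% larger.

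**Step 5. Single-voxel peaks under whole-brain family-wise control.** The number of tests is an assumption, so a range is needed. With Bonferroni, the per-voxel level is the family-wise level divided by the number of tests. Power with 40 per group (t to F):

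| Assumed tests | Family-wise 0.005 | Family-wise 0.05 |
|---|---|---|
| 1,000 | 2.8-3.4% | 8.6-9.7% |
| 2,000 | 1.9-2.4% | 6.2-7.2% |
| 5,000 | 1.2-1.5% | 4.0-4.7% |
| 50,000 | 0.3-0.4% | 1.2-1.5% |

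These figures also assume that the implied effect applies at one voxel. They do not describe cluster inference or regional means.

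**The case against.** - **The 0.05 could belong to another analysis.** The abstract names MoCA as primary, and neuropsychological data are tested at 0.05. That reading is possible, but the document does not state it. The sizing paragraph rests on two references for similar endpoints, and the document uses both in a perfusion context: one as the perfusion white paper in the 3D-pCASL section, the other for perfusion findings in the Discussion. This points towards imaging without proving it.
- **Not every imaging test is clearly at 0.005.** This stands. The CBF section sets corrected P<0.05, and whether 0.005 extends to the scalar FreeSurfer volumes is not said. It narrows the claim and adds a contradiction to resolve. It does not attach the 80% to the image tests.
- **The effect is back-solved.** This also stands, and is why the Dunnett figure is a range and not a single value. Every variant still falls well short of 80%.
- **Stronger readings that a reader might infer.** One is that voxel-wise power is below 2%. That needs more than about 2,000 to 3,000 assumed tests and single-voxel inference; the document gives no such number, and for CBF it also plans a cluster extent and regional means. Another is that the power sum itself is wrong; without a stated effect, no miscalculation can be shown. A third is that the unstated effect and SD, the use of the white paper as a sizing reference, or 53 in place of 54 are defects in their own right. A condensed article commonly leaves the first to the full protocol, the second turns on a source not at hand, and the third is a quarter of a participant.

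**Conclusion.** The point holds as an internal inconsistency. The stated 80% at alpha 0.05 does not apply to image tests run at P<0.005. With 40 evaluable per group and the effect implied by the plan's own n, alpha and power, the figure is about 48-49% by t or F and about 37-53% by Dunnett. With no drop-out it is about 65-67% (t or F). These results rest on the back-solved effect and on reading 0.005 as the level for the group comparison of a single measure. If 0.005 is instead a whole-brain voxel-wise level, power for a single voxel is far lower: about 0.3-3.4% for an assumed 50,000 down to 1,000 tests. Separately, the two thresholds given for imaging, 0.005 in the statistics section and corrected 0.05 for voxel-wise CBF, contradict each other.

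**What to change.** 1. Reconcile the 3D-pCASL data analysis section with the statistics section so that one imaging threshold applies, and say which correction it carries (Dunnett contrasts, voxels or clusters).
2. Restate the power, or the minimum detectable difference, for the imaging test at that threshold and multiplicity rule. If 0.005 is kept, for example: a two-sample comparison with 40 per group has 80% power only for d of about 0.84.
3. Alternatively, state that the 80% applies only to analyses tested at 0.05, and name them.

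The cost is rewording two paragraphs. No extra enrolment is needed. The downside is a less favourable stated power for imaging.

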### Subject

#### Subjects inclusion

Participants with a minimum of the senior high school education will be prospectively recruited in one of the three groups: healthy control (HC), prodromal diabetes, or T2DM group according to the following inclusion criteria. *HC group*: Individuals with normal HbA1c and blood glucose level and no evidence of T2DM will be recruited into this group. Their fasting plasma glucose (FPG) levels are < 5.6 mmol/L, and 2 h fasting glucose (PG) levels for oral glucose tolerance test (OGTT) are < 7.8 mmol/L. *Prodromal diabetes group*: Individuals who have the impaired fasting glucose (IFG, FPG 5.6-6.9 mmol/L) or impaired glucose tolerance (IGT, 2 h PG for OGTT 7.8-11.1 mmol/L, but not meet the diagnostic criteria for T2DM will be recruited in this group. *T2DM group*: Individuals will be recruited into this group if they fall in any one of the following criteria: (1) FPG ≥ 7.0 mmol/L or, (2) 2 h PG for OGTT ≥11.1 mmol/L or, (3) random PG ≥11.1 mmol/L in the presence of typical diabetes symptoms.

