### Secondary outcome measures

*Evaluation of obesity and the changes in the state of obesity at 2.5 years*. Simple evaluation of obesity will include: body mass index will be calculated as the weight (kg) divided by the square of the height (m^2^). Waist circumference will be taken as the minimum circumference between the umbilicus and xiphoid process and measured to the nearest 0.5 cm. [Time Frame: subjects will be assessed six times (once half a year, up to 2.5 years)]*Metabolic characteristics and their changes at 2.5 years*. Simple metabolic characteristics will include: oral glucose tolerance test, C peptide releasing test and insulin releasing test, homeostasis model assessment of insulin resistance,insulin secretion of homeostasis model assessment and homeostasis model assessment-β. What’s more, cardiovascular risk factors (e.g., albumin, creatinine, total cholesterol, low density lipoprotein (LDL)- and high density lipoprotein (HDL)-cholesterol, triglycerides, glycosylated hemoglobin) will be assessed. [Time Frame: subjects will be assessed six times (once half a year, up to 2.5 years)]*Mental health and the changes in the scores of the scales at 2.5 years*. To evaluate the mental health, a series of psychiatric evaluation scale (e.g., MMSE, MoCA,HAS, SDS, WHOQOL) will be assessed. [Time Frame: subjects will be assessed six times (once half a year, up to 2.5 years)]*Lifestyle and its changes at 2.5 years*. Lifestyle specifics, including alcohol consumption, smoking behavior and mobility and exercise habit will be obtained. At the same time, quality of life will be obtained through a questionnaire. [Time Frame: subjects will be assessed six times (once half a year, up to 2.5 years)]

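### The obesity and metabolic secondary outcomes have only an unadjusted overall three-group test, although the same paragraph already specifies gender and age adjustment for the neuropsychological scores

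*Protocol article*

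**What the plan says.** All the analysis text is in the protocol article, under Sample size calculation and statistics.

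- The paragraph opens by naming the data: "Demographic clinical, laboratory, cognitive, and neuropsychological data will be analyzed using SPSS 22.0".
- For all of these, one-way analysis of variance or a chi-square "test will be used to explore differences of these data among three groups (HC, prodromal diabetes and diabetes"). No covariate is named.
- The next sentence adds adjustment for one family only: "Neuropsychological difference among them will be performed with analysis of covariance (ANCOVA) using demographic factors (gender, age, and years of education) as covariates".
- The sentence after that says that post-hoc "comparisons will then be performed with all demographic factors (gender, age, and years of education) as covariates". It names no outcome.

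The Secondary outcome measures section lists an obesity family (body mass index and waist) and a metabolic family that includes creatinine and HDL-cholesterol. Both levels and changes at 2.5 years are of interest. Waist is a measured quantity, not a category: "Waist circumference will be taken as the minimum circumference between the umbilicus and xiphoid process and measured to the nearest 0.5 cm". The statistics section does not name the obesity measures. They come under it only as clinical data.

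Under Subjects inclusion, participants "will be prospectively recruited in one of the three groups: healthy control (HC), prodromal diabetes, or T2DM group" by their glucose values, with a minimum level of education. The article describes no matching or balancing on sex or age.

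**The concern.** The groups are not randomised, so nothing in the design makes the share of men equal across them. The plan treats gender and age as factors to adjust for when these same groups are compared on neuropsychological scores. It gives no reason to leave them out when the groups are compared on waist, creatinine or HDL-cholesterol.

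If a measure differs between men and women, an unadjusted overall test has two weaknesses. The variation between the sexes goes into the error term, which costs power. Any difference in the share of men goes into the group contrast, so a reported difference between glycaemic groups could partly reflect sex mix.

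**Working it through.** **Inputs from the article.** "A sample size of 40 patients per group will be suitable with a power of 0.8, an alpha significance level of 0.05 (two-side"), and, allowing for drop-out "at 25 %, into account, the total sample size is 53 in each group". Check: 40 / (1 − 0.25) = 53.3, which agrees with the stated 53. The 40 itself cannot be rebuilt, because no effect size or SD is given.

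**Assumptions (not in the article).** The sex gap d is taken as 0.5, 1.0 or 1.5 within-sex SD. The shares of men in the three groups are taken as 50/50/50, 40/50/60 or 35/50/65%. The outcome is a level at one visit.

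**Step 1: a reference effect.** For three groups of 40 (N = 120, alpha 0.05), the noncentral F gives 80% power at Cohen's f = 0.287. With equally spaced means the spread is f × √6 = 0.287 × 2.449 = 0.70 SD, that is, means of 0, 0.35 and 0.70. This is only a yardstick, since the article does not size the study on these outcomes.

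**Step 2: power with balanced sexes.** The share of variance due to sex is R² = 0.25d² / (1 + 0.25d²).

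- d = 0.5: R² = 0.0625 / 1.0625 = 0.06
- d = 1.0: R² = 0.25 / 1.25 = 0.20
- d = 1.5: R² = 0.5625 / 1.5625 = 0.36

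Without a sex term the effective f is 0.287 × √(1 − R²). At d = 1.0 it is 0.287 × 0.894 = 0.257, and power is about 70%. At d = 1.5 it is 0.287 × 0.8 = 0.230, and power is about 58% (56 to 60% depending on whether it is simulated or taken from the formula). With a sex term, power is about 80%.

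Read the other way, if the unadjusted test is the one with 80% power, adding a covariate with R² = 0.20 raises power to 88.4%. For R² from 0.05 to 0.40 the range is 82.1% to 95.7%. Using three covariates instead of one costs less than 0.1 point.

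**Step 3: spurious contrast when the sexes are not balanced.** The expected false difference between the outer groups is (difference in share of men) × d.

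- 40/50/60%: 0.20 × 1.0 = 0.20 SD, or 0.20 × 1.5 = 0.30 SD
- 35/50/65%: 0.30 × 1.0 = 0.30 SD, or 0.30 × 1.5 = 0.45 SD

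These compare with the 0.70 SD spread of Step 1.

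**Step 4: false rejection with no true group effect.** Simulated, 40 per group, one-way ANOVA at 5%. The figures depend on whether the counts of men are fixed at the stated shares or each participant's sex is drawn at random with those shares, so both are shown.

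| Men, % | Sex gap, SD | Fixed counts | Random draws |
|---|---|---|---|
| 40/50/60 | 0.5 | about 6% | about 6% |
| 40/50/60 | 1.0 | 6–7% | 10% |
| 40/50/60 | 1.5 | 7–8% | 14% |
| 35/50/65 | 0.5 | 7% | 8% |
| 35/50/65 | 1.0 | 13% | 17–18% |
| 35/50/65 | 1.5 | 20–21% | 28% |

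ANCOVA with a sex term stays at about 5% in every row. With equal shares the unadjusted test rejects in about 5% under random draws and is conservative under fixed counts (2.4% at 1.0 SD). A larger sample does not cure the imbalance: with 53 per group and fixed counts at 35/50/65%, false rejection is 15.4% (1.0 SD) and 25.9% (1.5 SD).

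**The case against.** **The ANOVA is descriptive.** Its wording is exploratory. It covers demographics, and it also covers the neuropsychological scores before their ANCOVA is named. So the paragraph does not cleanly divide outcomes into adjusted and unadjusted families. This stands as a reading of intent. But for the obesity and metabolic outcomes no other overall group comparison is stated, and the paragraph sets P < 0.05 as significant.

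**The post-hoc sentence may already adjust.** It carries the covariates and names no outcome. It follows the ANCOVA sentence and most naturally belongs to it, but a wider reading is open. A reader might infer that these outcomes get no adjustment anywhere, and the text does not establish that. On the wider reading the pairwise comparisons are adjusted and only the overall test is not.

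**Silence on matching is not a statement of no matching.** That is right for a condensed article. A reader might infer that the groups are known to be unbalanced on sex, and the document does not say so. All participants come from one centre and are aged 40–60, which narrows age differences but does not control the sex mix.

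**The size is assumed, and covers levels only.** The article gives neither sex gaps nor sex mix, and the larger figures need a 30-point spread in the share of men. For within-person change, which the article also lists, a constant sex difference cancels. Measures that define the groups, or lie close to them, are unlikely to change their conclusion. All of this stands and limits the point to levels of sex-dependent measures.

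**Conclusion.** The point holds in a limited form. The only overall three-group test stated for the obesity and metabolic secondary outcomes is unadjusted, and an adjusted analysis is already specified in the next sentence for other outcomes. For levels of sex-dependent measures this costs about 10 points of power at a sex gap of 1.0 SD and about 22 at 1.5 SD, even with balanced sexes. It lets a sex imbalance raise false rejection from 5% to somewhere between 6 and 28%, depending on the gap, the imbalance and the sampling model.

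A reader might infer that the planned comparisons are biased as they stand. The documents do not support that: the inflation arises only if the groups turn out to differ in sex mix. Nor does it extend to every outcome in the two families. The outcomes are secondary, so this is a free improvement, not a flaw that threatens the study's main conclusions.

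**What to change.** In Sample size calculation and statistics:

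1. Extend the ANCOVA already specified, with at least gender and age as covariates, to the continuous obesity and metabolic secondary outcomes.
2. Keep one-way ANOVA and chi-square for describing the demographics of the groups.
3. State that the covariate-adjusted post-hoc comparisons cover these outcomes too.

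Cost: a sentence or two. Gender and age are already needed for the neuropsychological ANCOVA, so no new data are required. The two covariates take two error degrees of freedom: 120 − 3 = 117 becomes 115.
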